### **12.1.3.6 Intensity / AE grading**

Grade is used to denote the severity of the adverse event. The NCI-CTCAE v5.0, will be used as reference for AE grading in this trial. If the term does NOT appear in the CTCAE, the AE is graded using the following categories:

- **Mild (Grade 1):** minor; no specific medical intervention; asymptomatic laboratory findings only, radiographic only; marginal clinical relevance
- **Moderate (Grade 2):** minimal intervention; local intervention; noninvasive intervention (packing, cautery),
- **Severe (Grade 3):** significant symptoms requiring hospitalization or invasive intervention; transfusion; elective interventional radiological procedure; therapeutic endoscopy or operation). The term “severe” is often used to describe the intensity (severity) of a specific event. This is not the same as “serious,” which is based on patient/event outcome or action criteria (see section 11.2).
- **Life-threatening or disabling (Grade 4):** complicated by acute, life-threatening metabolic or cardiovascular complications such as circulatory failure, hemorrhage sepsis. Life-threatening physiologic consequences; need for intensive care or emergent invasive procedure; emergent interventional radiological procedure, therapeutic endoscopy or surgery.
- **Death or Fatal (Grade 5)**

|                                                                                   |                    |                                                                      |
|-----------------------------------------------------------------------------------|--------------------|----------------------------------------------------------------------|
| [figure not shown] | DOCUMENT    | Protocol ID : MPOH05
EudraCT N° : 2019-004253-89
Version: 10.0 |
|                                                                                   | CIMON STUDY | Date : 04 MAY 2021
Page 47 / 70                                   |

### **12.1.3.7 Causality assessment**

Attribution of causality is the determination of whether an adverse event is related to a medical treatment or procedure; categories are:

- Certain: the AE is clearly related to the treatment or procedure.
- Probable: the AE is likely related to the treatment or procedure, there are good reasons and sufficient documentation to assume a causal relationship.
- Possible: the AE is may be related to the treatment or procedure; a causal relationship is conceivable and cannot be dismissed.
- Unlikely: AE or laboratory test abnormality, with a time to drug that makes a relationship improbable (but not impossible). Diseases or other drugs provide plausible explanations
- Not related: the AE is clearly NOT related to the treatment or procedure. The event is most likely related to etiology other than the treatment or procedure.

Causality will be grouped by categories:

- Reasonable possibility: where the AE is clearly (certain), likely (probable) or may be (possible) related to the treatment or procedure. Such events would be considered adverse reactions.
- No reasonable possibility: where the AE is clearly NOT (not related) or doubtfully (unlikely) related to the treatment or procedure.

### **12.1.3.8 Outcome**

The event outcome is mandatory and should be recorded as soon as it gets resolved, where appropriate when the subject has completed the protocol at the latest. The outcome should be one of the following:

- **Recovering:** the AE is still ongoing with an improvement
- **Not yet recovered:** the AE is still ongoing when the subject has completed the protocol.
- **Recovered:** fully recovered or by medical or surgical treatment the condition has returned to baseline level.
- **Recovered with sequelae:** as a result of the AE, the subject suffered persistent and significant disability/incapacity (e.g. became blind, deaf, paralyzed). Any AE recovered with sequelae should be declared as an SAE.
- **Fatal:** any AE resulting in death should be declared as an SAE

### **12.1.3.9 Follow-up**

The Investigator should take all appropriate measures to ensure the safety of the subjects, notably he/she should follow up the outcome of any Adverse Events (clinical signs, laboratory values or other, etc.) until the return to normal or consolidation of the subject's condition;

In case of any Serious Adverse Event, the subject must be followed up until clinical recovery is complete and laboratory results have returned to normal, or until progression has been stabilized. This may imply that

|                                                                                   |                    |                                                                      |
|-----------------------------------------------------------------------------------|--------------------|----------------------------------------------------------------------|
| [figure not shown] | DOCUMENT    | Protocol ID : MPOH05
EudraCT N° : 2019-004253-89
Version: 10.0 |
|                                                                                   | CIMON STUDY | Date : 04 MAY 2021
Page 48 / 70                                   |

follow-up will continue after the subject has left the Clinical Trial and that additional investigations may be requested by the pharmacovigilance officer.

In case of any Serious Adverse Event brought to the attention of the Investigator at any time after the clinical trial with a reasonable possibility, this should be reported to the pharmacovigilance officer.

### **12.1.3.10 Pregnancy**

Pregnancy will be recorded as an AE in all cases. It will be qualified as an SAE only if it fulfills SAE criteria.

In the event of pregnancy, the Investigator inform immediately (i.e. within 24 hours), even not fulfilling a seriousness criterion using the corresponding pages in the CRF (to be sent) or the screens in the e-CRF, following the same process as described for the Serious Adverse Events.

Follow-up of the pregnancy will be mandatory until the outcome has been determined.

### **12.1.4 Safety Committee (SC)**

The tolerability of the study **will be evaluated for every patient by the Committee, once for each cohort.**

The events of interest during MaaT033 treatment are:

- Infections and infestations
- GI disorders

The responsibilities of the committee and its members are:

- To review tolerability of MaaT033 different dose regimen at the end of different cohort follow up (see design of the study) and make recommendations to continue, modify or terminate the study
- To ensure the ongoing safety for study subjects
- To review all study documents provided by the sponsor
- To be the referee for the imputability of adverse reactions on behalf of sponsor

#### **12.1.4.1 Tolerability consideration:**

Investigators will be trained regarding the mode of action of the investigational medicinal product and to be particularly attentive to any signs of toxicity.

**Dose Limiting Toxicity (DLT):** Based on the literature and our preclinical data, no particular toxicity is expected. Toxicity events will be defined as any at least possibly related adverse event grade  $\geq 3$  based on CTCAE v5.0 criteria. Due to the specific therapeutic protocol that blood cancer patients usually follow, the follow-up of patients in term of DLT is set from V1 (end of neutropenia) to V3 (start of a new chemotherapy cycle, or consolidation). Nevertheless, there are some anatomical or physiological system events that will be considered as expected in the context of patients with AML or HR-MSD, and thus not related to the treatment. Such events will only be considered DLT when grade  $> 3$ :

- Blood and lymphatic system disorders (DLT when grade 4 or 5)
- Immune system disorders (DLT when grade 4 or 5)

Depending on the number of DLTs, the dose is either escalated (0 DLTs) or de-escalated ( $\geq 2$  DLTs). Due to our specific drug activity assessment goals, cohorts 2 to 5 will systematically be expanded with 3 extra patients (0 or 1 DLTs) each.

|                                                                                   |                    |                                                                      |
|-----------------------------------------------------------------------------------|--------------------|----------------------------------------------------------------------|
| [figure not shown] | DOCUMENT    | Protocol ID : MPOH05
EudraCT N° : 2019-004253-89
Version: 10.0 |
|                                                                                   | CIMON STUDY | Date : 04 MAY 2021
Page 49 / 70                                   |

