#### 8.2.2 **Decision rules for choice of dose regimen**

This study has for objective to assess MTD and MAD in term of MaaT033 activity (bacteria engraftment). Activity assessment requires a minimum of 6 patients to allow for a sufficient robust analysis of engraftment.

Activity and tolerability assessment may depend both on duration of treatment and/or daily dose. Therefore, the study will assess both 7 days and 14 days dose regimen, for the 3 capsules/day dosing.

Therefore, the study will ensure that a minimum of 6 patients is included for all the dose regimen that do not reach the MTD.

Definitions:

**Minimal Active Dose (MAD):** Minimum dose regimen that will lead to a minimal activity (1 or 2, cf chapter 8.3.2) of the product.

|                                                                                   |                    |                                                                      |
|-----------------------------------------------------------------------------------|--------------------|----------------------------------------------------------------------|
| [figure not shown] | DOCUMENT    | Protocol ID : MPOH05
EudraCT N° : 2019-004253-89
Version: 10.0 |
|                                                                                   | CIMON STUDY | Date : 04 MAY 2021
Page 24 / 70                                   |

**Dose Limiting Toxicity (DLT):** Toxicity event will be defined as any related adverse event grade >3 based on CTCAE v5.0 criteria for:

- Blood and lymphatic system disorders (DLT when grade4 or 5)
- Immune system disorders (DLT when grade4 or 5)

And any related adverse event grade  $\geq 3$  for all other system organ.

**Maximal Tolerated Dose (MTD):** Maximal dose for which only 0 or 1 patient do experience limiting toxicity out of a cohort of 6 patients.

The study has an adapted “6 dose titration” escalation design to allow for assessment of tolerability (research of the Maximal Tolerated Dose) and of activity (research of Minimal Active Dose):

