- **5th level of dose:** 6 patients will be treated with 9 capsules/day for 7 days. The Safety Committee (SC) will evaluate occurrence of Limiting Toxicity after the 6 patients will have completed V3. If two patients or more experiment a DLT, the study will be stopped and MTD will be considered as dose level 4. If one patient or less experiments a DLT, the MTD will be considered dose level 5.

**In any of the cohort 2 to 5, if any safety signal suggesting potential DLT is reported in 2 or more patient before the end of the inclusion of all patient of the cohort, inclusion of subsequent patient will be suspended and ad hoc meeting of the DSMB will be hold with all available information to assess those potential DLT and decide on the continuation or stopping the study.**

**A 24-hour gap should be respected between inclusions of the first 3 patients of each cohort to consider potential early or delayed toxicities.**

|                                                                                   |                    |                                                                      |
|-----------------------------------------------------------------------------------|--------------------|----------------------------------------------------------------------|
| [figure not shown] | DOCUMENT    | Protocol ID : MPOH05
EudraCT N° : 2019-004253-89
Version: 10.0 |
|                                                                                   | CIMON STUDY | Date : 04 MAY 2021
Page 25 / 70                                   |

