### **8.3 ENDPOINTS AND EVALUATIONS**

The studied procedure will be considered as safe if:

No severe SAE related to treatment procedure has been documented.

All patients' case profiles will be reviewed by a committee composed by 3 physicians. The main task of this committee will be to evaluate collected data and to give an opinion on treatment safety. The committee will analyze all treatment emergent AE(s) and propose categorization as treatment-related or not. In case of disagreement, majority (2 out of 3) committee's opinion will be considered as final decision.

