The cohort review committee may permit enrollment of additional patients in any cohort to ensure that there is the required number of patients with evaluable DLTs at each dose level cohort.

The cohort review committee may review and delay enrollment into the next dose cohort based on observed toxicities.

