#### **12.1.4.3 Recommended Phase 2 Dose RP2D**

Once the MTD or MED is determined, or once the highest dose has been reached without declaring an MTD, the cohort review committee will select the recommended dose for the following studies with MaaT033 (recommended Phase 2 dose; RP2D).

RP2D usually is the highest dose with a pre - specified DLT rate. In this study, this dose will be the MTD, a dose below the MTD, or any other dose suggested upon clinical evaluation or all available safety, activity and efficacy parameters.

In case an RP2D is selected that is not the MTD, a minimum of 6 patients will need to be treated and followed-up for 7 days at this dose level (with a maximum of 1 DLT observed), before declaring it as the RP2D.

|                                                                                   |                    |                                                                      |
|-----------------------------------------------------------------------------------|--------------------|----------------------------------------------------------------------|
| [figure not shown] | DOCUMENT    | Protocol ID : MPOH05
EudraCT N° : 2019-004253-89
Version: 10.0 |
|                                                                                   | CIMON STUDY | Date : 04 MAY 2021
Page 50 / 70                                   |

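### Related grade 3 immune system disorders are never DLTs, so a severe allergic reaction to the capsule classed there would go uncounted, for a reason that does not apply to it

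*Protocol*

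**What the plan says.** Section 8.2.2 of the Protocol sets two thresholds. For most organ classes a related event is a DLT from grade 3. For two classes the bar is higher: "Toxicity event will be defined as any related adverse event grade >3 based on CTCAE v5.0 criteria for" blood and lymphatic system disorders and immune system disorders. The second entry reads "Immune system disorders (DLT when grade4 or 5").

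Section 12.1.4.1 starts from at least possibly related events of grade 3 or higher and repeats the exemption: "Immune system disorders (DLT when grade 4 or 5"). It gives the only justification, that certain events "will be considered as expected in the context of patients with AML or HR-MSD, and thus not related to the treatment".

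The DLT count is used in four places:
- Cohort 1 (8.2.2): no DLT in three patients means escalation to level 2; one or more sends the decision to the Safety Committee.
- Cohorts 2 to 5 (8.2.2): DLTs in two or more of six patients stop the study.
- MTD (8.2.2): the highest dose with limiting toxicity in at most one of six patients.
- An RP2D other than the MTD (12.1.4.3): at least six patients treated, "with a maximum of 1 DLT observed".

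Allergy appears elsewhere. Section 9.2 excludes patients with known allergy or intolerance to three named substances, and 11.4.1 gives allergic reactions to the study drug as an example of an event that can lead to discontinuation.

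**The concern.** The exemption and its reason do not match. The reason concerns events that the patient's condition explains. The exemption, as 8.2.2 words it, concerns events already attributed to the product. A severe allergic reaction to an orally given, donor-derived product is the plainest case where the two part: the capsule would be the cause, and AML or HR-MDS would not explain it.

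The primary objective is the maximal tolerable dose. If a related, severe reaction of this kind is left out of the DLT count, escalation can proceed, and an MTD or RP2D can be declared, on a count that omits it.

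**Working it through.** The protocol gives no figure on this point, so there is none to reproduce. The check is first of the text, then of the size.

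**Text**

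1. Read alone, 12.1.4.1 could be taken to exempt only events expected from the disease. Section 8.2.2 has no such limit: relatedness comes first, then the threshold. Section 12.1.4.2 refers to 8.2.2 for the escalation rules, so its wording governs.
2. The causality scale in 12.1.3.7 already removes disease-explained events. An event for which disease or other drugs offer a plausible explanation is graded unlikely, and unlikely is grouped with no reasonable possibility. DLTs must be at least possibly related. The class exemption therefore acts only on events the assessors have not put down to the disease.
3. Only known allergy is screened out in 9.2, so a first reaction remains possible.
4. The protocol does not list the terms in the immune system disorders class. A reaction classed elsewhere would already be a DLT at grade 3 under 8.2.2. The point is conditional on that classification.

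**Nearest data (section 6.4)**

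Patients given MaaT012 or MaaT013 by enema: 6 + 20 + 30 = 56, with 0 related SAEs. The 2 + 3 = 5 SUSARs listed for them are colonic perforation, intestinal ischemia and three cases of sepsis; none is allergic. The one-sided 95% upper bound for 0 of 56 is 1 − 0.05^(1/56) = 0.052. These are SAEs after enemas, not grade 3 events after capsules, so the bound is only a guide to the range.

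**Size**

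Let p be the true rate of related grade 3 allergic reactions. The values 2% and 5% are assumptions. With X ~ Bin(6, p):

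- P(X ≥ 1) = 1 − (1 − p)^6
- P(X ≥ 2) = 1 − (1 − p)^6 − 6p(1 − p)^5
- Cohort 1: P(at least 1 of 3) = 1 − (1 − p)^3
- At least one of cohorts 2 to 5 with X ≥ 2, same rate in each: 1 − [1 − P(X ≥ 2)]^4

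| p | at least 1 of 3 | at least 1 of 6 | at least 2 of 6 | any of four cohorts with at least 2 |
|---|---|---|---|---|
| 2% | 0.059 | 0.114 | 0.0057 | 0.023 |
| 5% | 0.143 | 0.265 | 0.0328 | 0.125 |

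At the 5.2% bound, P(X ≥ 2) = 0.035.

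If other DLTs also occur, independently, at an assumed 5%, the chance of two or more in six is 0.0328 without the allergic events. Counting them:

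- p = 2%: patient-level rate 1 − 0.95 × 0.98 = 0.069, giving 0.0593, an increase of 0.0265.
- p = 5%: patient-level rate 1 − 0.95² = 0.0975, giving 0.1094, an increase of 0.0766.

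**The case against.** The strongest objection is that the classification of allergic reactions is not in the protocol. That is right, and the point is stated conditionally for that reason. It does not rescue the definition: if the class to which a reaction is coded decides whether the same severe reaction counts, the rule should settle the matter explicitly.

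Second, these patients receive many drugs, so attributing immune events is hard, and a higher threshold for a confounded class is a legitimate design choice. This stands for the class as a whole and is why the exemption should stay. It does not extend to a reaction that the assessors attribute to the capsule.

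Third, safeguards exist. The committee can recommend modifying or terminating the study (12.1.4), call ad hoc meetings, and "may review and delay enrollment into the next dose cohort based on observed toxicities" (12.1.4.2). Inclusions are suspended if "any safety signal suggesting potential DLT is reported in 2 or more patient" (8.2.2). One criterion for calling the procedure safe is "No severe SAE related to treatment procedure has been documented" (8.3). The primary criterion in 14.1.1 is drug related adverse events generally, and the RP2D may rest on all safety data (12.1.4.3). These reduce the risk. They are discretionary or partial, however: the suspension rule needs a potential DLT in two patients, which a grade 3 immune event does not clearly satisfy, and the criterion in 8.3 covers only serious events. None makes the event a DLT.

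Fourth, no allergic event is reported in the protocol's own data, and the rates used here are assumptions. That is true, and it is why the effect is called small.

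**Conclusion.** The concern holds. Both definitions exempt every related grade 3 immune system disorder, and the one reason offered does not reach an allergic reaction caused by the capsule. It rests on the assumption that such reactions would be classed as immune system disorders.

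The size is small. One uncounted event in a six-patient cohort is plausible at the assumed rates; two, which would change the stopping decision by themselves, are unlikely. A single event matters more in cohort 1, where it would end automatic escalation if counted, and in any cohort that already has one other DLT. It is a low-probability gap in a dose-finding rule and should be closed because closing it is cheap.

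**What to change.** Keep the class exemption. Add the same sentence to 8.2.2 and 12.1.4.1: any at least possibly related allergic, hypersensitivity or anaphylactic reaction of grade 3 or higher is a DLT, regardless of the organ class to which it is coded.

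The drafting cost is one sentence in two places. The operating cost is some added chance of stopping. From these events alone it is about 0.01 per six-patient cohort at 2% and 0.03 at 5%, or 0.02 and 0.12 over cohorts 2 to 5. With other DLTs at 5%, the addition per cohort is 0.03 and 0.08. Some of these stops could come from reactions to a concomitant drug in which the capsule cannot be ruled out. The Safety Committee's causality review, already foreseen in the protocol, is the place to limit that.

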- **1st level of dose for 1st cohort:** - 3 Patients will be treated with one capsule/day on day 1 and D7. The Safety Committee (SC) will evaluate occurrence of Limiting Toxicity after the 3 patients will have completed V3. If no patient experiments a DLT, the following cohort will use dose level 2 *i.e.* 1 capsule/Day for 7 days. If one or more patient experiment a DLT, the SC might consider study stop recommendation or cohort continuation. The purpose of this cohort is to assess feasibility of the whole procedure and check any unexpected tolerability issue that would prohibit continuation of the experimentation. As the dose schedule is not considered as sufficient enough to allow for any effective activity, it will not be considered for the choice of final dose.
- **2nd Level of dose (cohort2):** 6 patients will be treated with 1 capsule/day for 7 days. The Safety Committee (SC) will evaluate occurrence of Limiting Toxicity after the 6 patients will have completed V3. If no or 1 patient experiments a DLT, the following cohort will use dose level 3 *i.e.* 3 capsules/day for 7 days. If two or more patients out of 6 experiment a DLT, the study will be stopped.
- **3rd level of dose (cohort3):** 6 patients will be treated with 3 capsules/day for 7 days. The Safety Committee (SC) will evaluate occurrence of Limiting Toxicity after the 6 patients will have completed V3. If no or 1 patient experiments a DLT, the following cohort will use dose level 4 *i.e.* 3 capsules/D for 14 days and dose level 5 *i.e.* 9 capsules/day for 7 days. If two or more patients out of 6 experiment a DLT, the study will be stopped.
- **4th level of dose:** 6 patients will be treated with 3 capsules/day for 14 days. The Safety Committee (SC) will evaluate occurrence of Limiting Toxicity after the 6 patients will have completed V3. If no or 1 patient experiments a DLT, the following cohort will use dose level 5 *i.e.* 9 capsules/day for 7 days. If two or more patients out of 6 experiment a DLT, the study will be stopped. Of note, if 2 or more DLT are reported during the 7 first days of treatment, then the SC will re-assess cohort3 evaluation.

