#### **12.1.4.2 Cohort Review Meetings:**

**Ad-hoc meetings can be called at any moment if needed for Safety consideration (DSMB).**

The dose-escalation process will be monitored by a **cohort review committee (DSMB, see corresponding chapter 8.2.2. for the dose escalation rules)**.

A cohort review meeting will be organized once all patients at a specific dose level have completed the V1 to V3 DLT period to decide regarding dose escalation. A cohort review meeting will also be organized as soon as DLTs are observed in 2 or more patients to decide about stopping the dose escalation and confirming the Maximum Tolerated Dose (MTD) has been reached:

Cohort1: 3 first patients in this cohort will allow the assessment of a potential unexpected safety signal and will confirm feasibility of the procedure. The CRC will review patients after treatment completion of the 3 patients. Safety, tolerability and DLT events between V1 and V2 will be evaluated to take the decision on dose escalation.

Cohorts 2&3: These cohorts present a more classical posology (daily treatment of 1 and 3 capsules respectively) in the microbiome capsule category (see section introduction). The CRC will review patient tolerability after treatment completion of the 6 patients of the evaluated cohort, completed with follow up information from of the previous cohorts. Tolerability and DLT events between V1 and V3 will be evaluated to take the decision on dose escalation.

Cohorts 4&5: No more dose regimen escalation are expected. Tolerability of those patients will of course be closely monitored. Because cohort4 will first be completed, a SC will validate the step up to cohort5.

The focus of this meeting will be to review the overall patients' safety and to ensure all DLTs have been identified to decide escalation to the next dose level, or to confirm if the MTD has been reached.

At the time of the decision to escalate the dose, the cohort review committee may recommend one or more of the following with the aim of establishing an MTD and/or enhancing potential safety and tolerability:

- That additional medication is used
- That specific measures are taken in the treatment of side effects based on AEs and building upon the cumulated experience in their management
- That caution is exercised in patients presenting with conditions that may exacerbate any observed toxicities

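### The dose-escalation rules conflict: section 8.2.2 opens level 5 both together with level 4 and only after it, and section 12.1.4.1 prints a different rule for 1 and for 2 or more DLTs

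*Protocol*

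**What the plan says.** Section 7.1 makes the maximal tolerable dose the primary objective. Section 8.2.2 defines the MTD as "Maximal dose for which only 0 or 1 patient do experience limiting toxicity out of a cohort of 6 patients" and then gives a rule for each level.

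- **Levels 2 to 4, 0 or 1 DLT:** go to the next level. For level 2 the text is "If no or 1 patient experiments a DLT, the following cohort will use dose level 3".
- **Levels 2 to 4, 2 or more DLTs:** "If two or more patients out of 6 experiment a DLT, the study will be stopped".
- **Level 3, what follows:** after 0 or 1 DLT the next step is "3 capsules/D for 14 days and dose level 5", so two levels are named together.
- **Level 4, what follows:** level 5 is used only after the 6 patients at level 4 have completed V3 with 0 or 1 DLT.
- **Level 5:** "If two patients or more experiment a DLT, the study will be stopped and MTD will be considered as dose level 4". With 0 or 1 DLT, level 5 is the MTD.

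Section 12.1.4.1 gives its own summary: "Depending on the number of DLTs, the dose is either escalated (0 DLTs) or de-escalated" when there are 2 or more. It adds that "cohorts 2 to 5 will systematically be expanded with 3 extra patients (0 or 1 DLTs) each".

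Section 12.1.4.2 refers to 8.2.2 for the escalation rules. It calls a committee meeting once 2 or more patients have a DLT, to decide whether escalation stops and whether the MTD has been reached. On the last two cohorts it first says that no further escalation is expected, and then: "Because cohort4 will first be completed, a SC will validate the step up to cohort5".

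**The concern.** The committee has to turn a DLT count into an action, and the text gives more than one action for the same count. Three conflicts stand in the current version.

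1. **Opening of level 5.** Under the level 3 rule, patients can start 9 capsules a day, the highest daily dose, before anyone has reviewed level 4. Under the level 4 rule and 12.1.4.2 they cannot.
2. **One DLT.** Section 8.2.2 escalates. Section 12.1.4.1 mentions escalation only for 0 DLTs and attaches 1 DLT only to the expansion.
3. **Two or more DLTs.** Stopping the study, de-escalating, and meeting to decide whether escalation stops are different instructions.

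At stake are the dose that the next patients receive and, for the first conflict, the MTD that the trial reports.

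**Working it through.** **Total sample size.** Section 9.3 gives a maximum of 27 evaluable patients. One cohort of 3 and four of 6 give 3 + 4×6 = 27, which agrees. If the 3 extra patients in 12.1.4.1 bring a cohort from 3 to 6, the total is still 27. If they come on top of 6, it is 3 + 4×9 = 39, which does not agree. So the expansion sentence makes sense only as 3 + 3. That implies a look after 3 patients, whereas 8.2.2 schedules its review after all 6 have completed V3.

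**Opening of level 5.** Take DLT counts at levels 2, 3, 4, 5. The joint reading assumes that cohort 5 is completed and its own rule applied. The sequential reading assumes that the committee's re-assessment of cohort 3, foreseen in 8.2.2 when 2 or more DLTs at level 4 fall in the first 7 days, leaves level 3 standing.

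| Counts | Sequential (level 4 rule, 12.1.4.2) | Joint (level 3 rule) |
|---|---|---|
| 0, 0, 2, 0 | stopped at level 4; MTD = level 3 | MTD = level 5 |
| 0, 0, 2, 2 | stopped at level 4; MTD = level 3 | level 5 rule declares level 4 |
| 0, 0, 0, 2 | MTD = level 4 | MTD = level 4 |

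In the second row under joint opening, level 4 is declared the MTD with 2 DLTs in 6, although the definition in 8.2.2 allows at most 1.

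**Two or more DLTs.** The level below has already passed with at most 1 DLT in 6, so it remains the MTD whether the study stops, de-escalates or ceases escalating. At level 2 there is no lower cohort of 6, and this is so under every wording. The conflict changes the action, not by itself the MTD.

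**How often the disputed results occur.** The protocol gives no DLT rate. Assume independent patients and the same rate p at each level. For a cohort of 6:

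- P(0) = (1−p)^6
- P(1) = 6p(1−p)^5
- P(≥2) = 1 − P(0) − P(1)

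Joint and sequential opening give different MTDs when levels 2 and 3 pass and level 4 does not, which has probability [P(0)+P(1)]² × P(≥2).

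At p = 10%:

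- P(0) = 0.9^6 = 0.531
- P(1) = 6×0.1×0.9^5 = 0.354
- P(≥2) = 0.114
- P(different MTD) = 0.886² × 0.114 = 0.090

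| Assumed rate | Exactly 1 in 6 | 2 or more in 6 | MTD differs, joint vs sequential |
|---|---|---|---|
| 1% | 6% | 0.1% | 0.1% |
| 2% | 11% | 0.6% | 0.6% |
| 5% | 23% | 3% | 3% |
| 10% | 35% | 11% | 9% |
| 20% | 39% | 34% | 15% |

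**If 12.1.4.1 meant 0 of 6.** This is an assumed literal reading, because the section states no denominator. At p = 10%, the chance to clear levels 2 to 4 would be 0.531³ = 15%, against 0.886³ = 70% under 8.2.2.

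**The case against.** The strongest defence is that 12.1.4.2 sends the reader to 8.2.2 for the escalation rules, and 8.2.2 covers 0 or 1 and 2 or more DLTs at levels 2 to 5 and defines the MTD. On that view 12.1.4.1 holds only a leftover summary. Much of this stands: 8.2.2 probably governs. It does not remove the different rule printed in the committee's own section, and it cannot settle the level 3 rule against the level 4 rule, since both are in 8.2.2.

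A reader might infer that 12.1.4.1 forbids escalation after 1 DLT in 6, which would make the 15% against 70% comparison a property of the plan. The text does not support that. It names no denominator, gives no order to hold at 1 DLT, and can be read as a 3 + 3 remnant that fits the total of 27. The reading that remains still implies a look after 3 patients that 8.2.2 does not schedule. The 24-hour gap between the first 3 inclusions and the suspension after 2 potential DLTs are not such a look.

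The assumed rates may also be too high. Section 12.1.4.1 expects no particular toxicity, and the table in section 6.4 shows 1 related SAE in 81 patients given sister products. That is not a DLT rate, but it is a reason to show the low end. At 1% to 2% the disputed counts are uncommon.

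On joint opening, three texts are sequential (the level 4 rule, 12.1.4.2 and, by implication, the level 5 fallback to level 4) and one clause is not. That favours sequence as the intention. The clause remains in force as written.

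**Conclusion.** The point holds: the escalation rules contradict each other in the current text and must be reconciled.

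The most consequential conflict is inside 8.2.2. Joint opening lets the highest daily dose start before level 4 is reviewed, can change the MTD, and with counts 0, 0, 2, 2 yields a declared MTD that breaks the protocol's own definition. At the assumed rates of 1% to 20% this affects 0.1% to 15% of trials.

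The 1-DLT conflict concerns a result with probability 6% to 39% per cohort over the same range. Its effect depends on how 12.1.4.1 is read. The conflict at 2 or more DLTs changes what is done with patients, and the 12.1.4.2 wording is a meeting held to decide, not a third fixed rule.

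A reader might conclude that the MTD cannot be derived from the protocol at all. That goes too far: with 8.2.2 as the governing section and cohorts run in sequence, it can. These figures rest on an assumed constant DLT rate and independent patients. The contradictions themselves rest on the text alone.

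**What to change.** Reconcile section 8.2.2 with sections 12.1.4.1 and 12.1.4.2 by keeping one algorithm, in 8.2.2, that states:

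- the action at 0, at 1 and at 2 or more DLTs, with the denominator;
- whether 6 patients are enrolled at once or as 3 + 3, and if the latter, what is reviewed after 3;
- the MTD declared after each stopping result, consistent with the definition in 8.2.2;
- which review opens level 5.

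Replace the rule text in 12.1.4.1 and 12.1.4.2 with a reference to it. Which rule to adopt is for the sponsor and the safety committee; no choice is proposed here.

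The cost is amendment text, its submission, and matching wording in the committee charter. The reconciliation itself needs no extra patients or procedures.
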